## Abstract

**Background:**

Commonly used noninvasive serological indicators serve as a step before endoscope diagnosis and help identify the high-risk gastric cancer (GC) population. However, they are associated with high false positives and high false negatives. Alternative noninvasive approaches, such as cancer-related features in cell-free DNA (cfDNA) fragments, have been gradually identified and play essential roles in early cancer detection. The integrated analysis of multiple cfDNA features has enhanced detection sensitivity compared to individual features.

**Objective:**

This study aimed to develop and validate an assay based on assessing genomic-scale methylation and fragmentation profiles of plasma cfDNA for early cancer detection, thereby facilitating the early diagnosis of GC. The primary objective is to evaluate the overall specificity and sensitivity of the assay in predicting GC within the entire cohort, and subsequently within each clinical stage of GC. The secondary objective involved investigating the specificity and sensitivity of the assay in combination with possible serological indicators.

**Methods:**

This is an observational case-control study. Blood samples will be prospectively collected before gastroscopy from 180 patients with GC and 180 nonmalignant control subjects (healthy or with benign gastric diseases). Cases and controls will be randomly divided into a training and a testing data set at a ratio of 2:1. Plasma cfDNA will be isolated and extracted, followed by bisulfite-free low-depth whole methylome sequencing. A multidimensional model named Thorough Epigenetic Marker Integration Solution (THEMIS) will be constructed in the training data set. The model includes features such as the methylated fragment ratio, chromosomal aneuploidy of featured fragments, fragment size index, and fragment end motif. The performance of the model in distinguishing between patients with cancer and noncancer controls will then be evaluated in the testing data set. Furthermore, GC-related biomarkers, such as pepsinogen, gastrin-17, and *Helicobacter pylori*, will be measured for each patient, and their predictive accuracy will be assessed both independently and in combination with the THEMIS model

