## Methods

### Study Objectives

This study aims to develop and validate a novel blood-based WMS method followed by the development of a multidimensional model for the analysis of various features of cfDNA specifically for early GC detection. We expect that this noninvasive liquid biopsy assay will be instrumental in distinguishing individuals with a high probability of GC. Individuals who receive a positive test result will subsequently obtain a confirmed diagnosis by gastroscopy. Conversely, individuals who receive a negative test result will considered as having a low probability of GC. For this group of patients, they would be recommended to undergo a deferred gastroscope, and possibly a repeated test annually.

The primary objective is to validate the overall diagnostic specificity and sensitivity of the model and additionally assess its performance in each clinical stage of GC. The secondary objective is to investigate the specificity and sensitivity of the model when combined with potential biomarkers such as PG, G-17, or *H pylori* levels, aimed at enhancing early GC detection.

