### Study Population

This study will enroll individuals who receive gastroscopy at Xijing Hospital of Air Force Military Medical University, Xi'an, China. Further, 2 groups will be formed based on the outcomes of gastroscopy: a malignant group and a nonmalignant group. The malignant group will include patients diagnosed with high-grade intraepithelial neoplasia or GC (more than 90 patients corresponding to >50% of patients in stages I and II), while the nonmalignant group will include both healthy individuals and patients with gastritis, gastric ulcers, gastric polyps, or other benign gastric diseases.

Clinical parameters, such as personal history, family history of digestive tract cancer, gastroscopic findings, and GC staging, will be systematically collected for each subject. Blood samples will be collected for WMS analysis, the results of which will be used to establish a GC diagnostic model.

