### Sample Size Estimate and Statistical Analysis

The sample size was estimated using the strategy mentioned by Negida et al [32]. Based on the abovementioned pilot study, the ensemble THEMIS model reached a sensitivity of 0.94 with 0.95 specificity (Figure 1). We expect that the new model integrating similar features as THEMIS will attain a sensitivity of at least 0.9. If we consider the 95% CI width of 0.08 (2-sided test α=.05), then at least 54 cancer cases will be required. If we also expect a certain amount of dropout, such as 10%, a minimum of 60 cases will be needed. The same number of patients will be enrolled in the nonmalignant control group for this case-control study. The plan is to allocate both groups of subjects by the same 2:1 ratio into training and testing data sets. Ensuring at least 60 cases and 60 controls within the testing data set, a total of 360 subjects (180 cancer cases and 180 controls) will be enrolled. This ensures that each group is composed of no fewer than 180 subjects. The malignant group and the control group will be matched by age and sex to minimize possible confounding factors (Figure 2).

The area under the curve, constructed with a receiver operator characteristic analysis calculated by the *pROC* package, will be used to evaluate individual classifier models as well as the ensemble model’s performance in distinguishing between cancer and noncancer conditions. Clinical diagnosis results, including but not limited to gastroscopy or pathological determinations, are considered the “gold standard.” The cancer risk threshold (cutoff value) will be determined based on the training data set. After that, the prediction performance of the established model will be evaluated in the testing data set in several aspects, including sensitivity, specificity, positive prediction value, and negative prediction value. These variables, as well as 95% CI, will be calculated using the *epiR* package. The Cohen κ score will be calculated with the *vcd* R package to demonstrate the concordance of the predicted results versus the pathological diagnostic results. A single-blind analysis will be applied, which means that the bioinformatics analysts will be blinded to whether the subjects have GC or not. The results are considered significant if the *P* value is <.05. All statistical analyses will be performed in R (version 3.6.3; R Core Team).

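### Stage-specific performance is in the primary objective, but the test set is sized only for overall sensitivity and the stated 2:1 split leaves its stage mix to chance

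*Protocol article*

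**What the plan says.** All references are to the protocol article.

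- **Objective.** The Abstract states, in a sentence that ends by naming the stages of disease: "The primary objective is to evaluate the overall specificity and sensitivity of the assay in predicting GC within the entire cohort, and subsequently within each". Study Objectives repeats it; the aim is to "validate the overall diagnostic specificity and sensitivity of the model and additionally assess its performance in each clinical stage of GC".
- **Sample size.** Sample Size Estimate and Statistical Analysis works from one quantity, overall sensitivity: "We expect that the new model integrating similar features as THEMIS will attain a sensitivity of at least 0.9". With a precision figure of 0.08 this gives 54 cases, then 60 after 10% dropout. Tripling for the 2:1 split gives 180 cases, with the same number of controls.
- **Split.** The Abstract (Methods) has: "Cases and controls will be randomly divided into a training and a testing data set at a ratio of 2:1". The sample size section adds: "The plan is to allocate both groups of subjects by the same 2:1 ratio into training and testing data sets". So the split is made within cases and within controls. No further factor is named.
- **Stage control.** Study Population sets an enrolment condition: "more than 90 patients corresponding to >50% of patients in stages I and II". No single stage has a target.
- **Matching.** The two groups will be "matched by age and sex to minimize possible confounding factors". The article does not say whether this is by pair or by frequency, or how it carries into the two data sets.

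**The concern.** The assay is meant for early detection, so the sensitivity a reader will look for first is the one in stages I and II. That figure, and the figure for each single stage, falls under the primary objective. Yet the sample size argument never considers how precise it will be, and no stated rule fixes how many test cases each stage contributes.

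The study has one locked test set and draws it once. If the draw gives few cases of some stage, the shortfall cannot be repaired afterwards without reopening the split. The same applies to the balance of healthy and benign controls. Including benign disease is the advance the Introduction claims over the pilot, whose controls had none.

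**Working it through.** **1. The plan's own figure.** For one proportion, n = z² p(1 − p) / d², with p = 0.90, z = 1.96 and d = 0.08:

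n = 3.8416 × 0.09 / 0.0064 = 54.02, against the stated 54.

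Dropout: 54 / 0.90 = 60. Total: 60 × 3 = 180 per group. The chain reproduces with 0.08 as the half-width; read as a full width (d = 0.04) it would give about 216. The calculation contains no stage term.

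**2. Stage counts in the test set.** If K of the 180 cases are in a given stage and 60 are drawn at random, the test count is hypergeometric with mean K/3 and variance 60 × (K/180) × (1 − K/180) × (120/179).

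For K = 45: mean 15, SD = √(60 × 0.25 × 0.75 × 0.670) = 2.75.

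| Cases enrolled in the stage | Mean in test set | 95% range |
|---|---|---|
| 20 (assumed) | 6.7 | 3 to 11 |
| 45 (assumed; four equal stages) | 15 | 10 to 20 |
| 90 (stages I-II together, at the enrolment floor) | 30 | 24 to 36 |

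Only the last row is tied to a figure in the article, which requires more than 90. With 91 the range is 24 to 37.

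**3. Precision at those counts.** Half-width = 1.96 × √(0.09 / n) at sensitivity 0.90:

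- n = 60: 0.076
- n = 30: 0.107
- n = 15: 0.152

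Exact (Clopper-Pearson) 95% intervals:

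- 13/15: 0.60 to 0.98
- 14/15: 0.68 to 1.00
- 27/30: 0.73 to 0.98

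**4. What stratifying changes.** A stage with 45 cases would give exactly 15 test cases instead of 10 to 20. The half-width at 15 stays at 0.152. Reaching ±0.08 in each of four stages would take 60 test cases per stage after dropout, so 4 × 60 = 240 test cases and 240 × 3 = 720 cases in all.

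**5. Effect of stage mix on overall sensitivity.** With 90 early cases enrolled, the early count in the test set has SD 3.17, or 3.17/60 = 0.053 as a proportion.

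- Assumed sensitivities 0.85 early and 0.95 late: 0.053 × 0.10 = 0.5 points (SD).
- Assumed 0.80 and 1.00: 0.053 × 0.20 = 1.1 points (SD).

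The ordinary sampling standard error at n = 60 is √(0.09 / 60) = 3.9 points.

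**6. Matching.** If matching were 1:1 and the two groups were split independently, a pair would be separated with probability 2 × (2/3) × (1/3) = 4/9, about 80 of 180 pairs. Under frequency matching, a random split keeps age and sex balance on average and leaves only chance differences.

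**The case against.** **Silence is not a defect.** A condensed article names few details of a data split and does not exclude stratification by stage. That is fair, so this is not raised as missing information. The point is that the method as stated can be improved at almost no cost, for an estimate that the article itself places in the primary objective.

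**Stage results are subordinate.** The article introduces them with words such as "additionally assess its performance in each clinical stage of GC". It sets no stage-specific hypothesis or success threshold. It plans 95% intervals, and the Discussion admits a modest cohort and promises larger prospective validation. This lowers the stakes, but it does not take stage out of the primary objective.

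**Stronger readings that the article does not support:**

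- *The split breaks the age-sex matching.* A reader might infer this, but it requires 1:1 pairs split independently. The article speaks only of groups being matched. What can be said is that preservation of the matching within each data set is not stated.
- *The split causes the small stage counts.* It does not. They follow from a 60-case test set divided among stages, and step 4 shows that stratifying leaves the intervals as wide.
- *Early-stage sensitivity rests on a handful of cases.* Stages I-II together should supply about 30, half the test cases. Only single stages could be that thin.
- *Chance stage mix distorts the overall estimate.* Under the assumed sensitivities in step 5 the effect is small beside sampling error.

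**Conclusion.** The concern stands in a limited form. Stage-specific performance is part of the primary objective, the test set is sized for overall sensitivity only, and the stated split does not control the stage mix of the 60 test cases. In 95% of splits a stage with 45 cases would contribute 10 to 20, one with 20 would contribute 3 to 11, and stages I-II together about 24 to 36.

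These ranges assume 180 cases with 60 drawn at random and no stratification beyond disease status. The single-stage sizes are illustrations, because the article fixes only that stages I-II exceed half.

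There are two separate issues. The variation in counts comes from the split and is curable. The imprecision comes from the test-set size: a half-width of about 0.15 at 15 cases is twice the 0.076 for the overall estimate. At the planned size it can be met only by asking less of single stages. This is an improvement worth making before the split is drawn; it does not invalidate the overall estimate.

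**What to change.** 1. **Split.** Stratify the 2:1 allocation by stage (I, II, III, IV) in cases and by healthy or benign status in controls. Balance it on age band and sex so that the group-level matching is kept in each data set. If the matching is by pair, keep pairs together. Cost: about one line in the allocation code. The split already needs case or control status, so whoever draws it can use stage without unblinding the bioinformatics analysts.
2. **Stage-level claim.** Make stages I-II versus III-IV the stage-level comparison within the primary objective. Report single stages descriptively, with counts and exact 95% intervals. Cost: single-stage results carry less weight; no extra recruitment.
3. **Optional support.** Add out-of-fold sensitivity by stage from nested cross-validation on the training cases, shown apart from the locked test result. With about 60 of 90 stage I-II cases in training, 54/60 would give an exact interval of 0.79 to 0.96. A figure based on all 90 early cases would not match an analysis limited to training cases. Cost: some computing, and the result describes the modelling procedure, not the single locked model.

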**Results:**

Recruitment began in November 2022 and will be ended in April 2024. As of August 2022,250 patients have been enrolled. The final data analysis is anticipated to be completed by September 2024.

**Conclusions:**

This is the first registered case-control study designed to investigate a stacked ensemble model integrating several cfDNA features generated from a bisulfite-free whole methylome sequencing assay. These features include methylation patterns, fragmentation profiles, and chromosomal copy number changes, with the aim of identifying the GC population. This study will determine whether multidimensional analysis of cfDNA will prove to be an effective strategy for distinguishing patients with GC from nonmalignant individuals within the Chinese population. We anticipate the THEMIS model will complement the standard-of-care screening and aid in identifying high-risk patients for further diagnosis.

**Trial Registration:**

ClinicalTrial.gov NCT05668910; https://www.clinicaltrials.gov/study/NCT05668910

**International Registered Report Identifier (IRRID):**

DERR1-10.2196/48247

## Introduction

Gastric cancer (GC) is one of the most commonly diagnosed digestive tract tumors, accounting for approximately 1.08 million new cases and an estimated 769,000 deaths in 2020 worldwide (7.7% of total cancer-related deaths), ranking fifth for age-standardized incidence and fourth for cancer-related mortality worldwide [1]. China is among the countries with the highest incidence rate of GC, although a gradual decline has been observed in recent years [2,3]. Early GC detection and its prompt treatment are strongly associated with improved prognoses for patients with GC. In Japan and South Korea, population-wide screening has been extensively implemented, resulting in effective diagnosis of tumors at early stages and improved survival rates [4]. Unfortunately, in China, most patients are diagnosed with advanced GC, probably owing to the large population and lack of standardized screening programs. While gastroscopy (upper gastrointestinal endoscope) and biopsy procedures conducted during gastroscopy remain the gold standard methods for GC diagnosis, gastroscopy is an invasive operation often met with poor compliance. Moreover, insufficient endoscopy physicians and endoscopic equipment, as well as the lack of a standardized endoscopic examination in China, present challenges for endoscopy to be used as a population-wide screening method [5].

Currently available noninvasive blood biomarker–based approaches could serve as a step before endoscope diagnosis and aid in identifying the high-risk GC population. However, these methods are associated with high false positives and high false negatives, which can potentially lead to overdiagnosis or underdiagnosis. Serological indicators such as *Helicobacter pylori* antibodies lack specificity for GC detection due to their strong association with atrophic gastritis and gastric ulcers [5]. Other indicators, including serum pepsinogen (PG), serum gastrin-17 (G-17), and MG7-Ag, are not recommended for standalone use due to their poor sensitivity and specificity [6]. A new GC score system based on age, sex, PG, G-17, and *H pylori* antibodies was introduced in China’s early GC screening process expert consensus [5]. While this new GC score system might exhibit improved prediction performance [7], the cost-benefit of its clinical application needs to be analyzed. Plasma tumor markers, such as carcinoembryonic antigen, cancer antigen (CA) 19-9, CA 72-4, CA 125, and CA 242, are linked to patient prognosis but are not suitable for early cancer detection [8]. Furthermore, circulating molecules such as miRNAs have garnered attention; however, their sensitivity and specificity are limited [9,10].

Rapid advancements in technology and analysis have identified cell-free DNA (cfDNA) as a new, simple, and noninvasive method for early cancer detection, offering enhanced specificity and sensitivity. The cancer-related features of cfDNA have been exploited in several aspects to distinguish cancer samples from healthy cases: (1) genetic alterations [11-13], (2) microsatellite instability [14], (3) hypermethylation or hypomethylation of certain genes [15,16] or across the genome [17-19], (4) chromosomal alterations [20], and (5) unique fragmentation patterns [21,22]. Among these aspects, identifying cfDNA genetic alterations poses a challenge due to the low fraction of mutation-bearing circulating tumor DNA (ctDNA) fragments in early-stage diseases or certain tumor types [23,24]. The combination of multiple features has enhanced detection sensitivity in comparison to relying on a single feature, as studied in kidney cancer [25], hepatocellular cancer, and pancreatic ductal cancer [26].

We have also previously developed a multidimensional ensemble model named Thorough Epigenetic Marker Integration Solution (THEMIS). This model integrates various cfDNA features, including methylated fragment ratio (MFR), chromosomal aneuploidy of featured fragments (CAFF), fragment size index (FSI), and fragment end motif (FEM), enabling highly sensitive early detection across a pan-cancer cohort [27]. In a subgroup comprising 114 patients with GC and 497 healthy controls, the THEMIS model showed an estimated area under the curve of 0.983 for the training data set (Figure 1A) and 0.986 for the test data set (Figure 1B). However, the fact that the model was trained on a pan-cancer cohort and the control group did not contain individuals with benign gastric diseases limits its predictive reliability for GC.

This study aimed to develop a highly sensitive GC-specific THEMIS model for the early detection of GC. This study’s design is illustrated in Figure 2. Patients with GC will be enrolled in the malignant group, while the control group will comprise not only healthy individuals but also participants with benign gastric diseases, such as gastritis, gastric ulcers, and gastric polyps. Consequently, a novel model will be developed to differentiate malignant cancer from nonmalignant gastric status. A nonbisulfite enzymatic whole methylome sequencing (WMS) assay [28] will be applied to ensure the preservation of methylation signals from the cfDNA alongside the molecular fragmentation profile. The sequencing data generated from cfDNA will then be analyzed across the abovementioned multiple dimensions, encompassing methylation patterns, chromosomal copy number alterations, and fragmentation profiles. In addition, GC-related biomarkers, such as PG, G-17, and *H pylori*, will be evaluated either independently or in combination with cfDNA features during model training to enhance the detection sensitivity. The overall clinical performance of the model, as well as its performance in each clinical stage, will be evaluated.

**Figure 1 figure1:**
[figure not shown]
Receiver operating characteristic curve analysis showing the cancer prediction performance of the THEMIS model in the GC subgroup: (A) training data set; (B) test data set. The AUC together with the 95% CI is shown. AUC: area under the curve; CAFF: chromosomal aneuploidy of featured fragments; FEM: fragment end motif; FSI: fragment size index; MFR: methylated fragment ratio; THEMIS: Thorough Epigenetic Marker Integration Solution.

**Figure 2 figure2:**
[figure not shown]
Flowchart of patient recruitment, sample collection, and statistical analysis strategy. cfDNA: cell-free DNA.

## Methods

### Study Objectives

This study aims to develop and validate a novel blood-based WMS method followed by the development of a multidimensional model for the analysis of various features of cfDNA specifically for early GC detection. We expect that this noninvasive liquid biopsy assay will be instrumental in distinguishing individuals with a high probability of GC. Individuals who receive a positive test result will subsequently obtain a confirmed diagnosis by gastroscopy. Conversely, individuals who receive a negative test result will considered as having a low probability of GC. For this group of patients, they would be recommended to undergo a deferred gastroscope, and possibly a repeated test annually.

The primary objective is to validate the overall diagnostic specificity and sensitivity of the model and additionally assess its performance in each clinical stage of GC. The secondary objective is to investigate the specificity and sensitivity of the model when combined with potential biomarkers such as PG, G-17, or *H pylori* levels, aimed at enhancing early GC detection.

### Study Population

This study will enroll individuals who receive gastroscopy at Xijing Hospital of Air Force Military Medical University, Xi'an, China. Further, 2 groups will be formed based on the outcomes of gastroscopy: a malignant group and a nonmalignant group. The malignant group will include patients diagnosed with high-grade intraepithelial neoplasia or GC (more than 90 patients corresponding to >50% of patients in stages I and II), while the nonmalignant group will include both healthy individuals and patients with gastritis, gastric ulcers, gastric polyps, or other benign gastric diseases.

Clinical parameters, such as personal history, family history of digestive tract cancer, gastroscopic findings, and GC staging, will be systematically collected for each subject. Blood samples will be collected for WMS analysis, the results of which will be used to establish a GC diagnostic model.

